### Study Participants

The participants are adult kidney transplant recipients with uncontrolled hypertension who have met the inclusion/exclusion criteria. Potentially eligible study patients were identified through weekly data extractions from the appointment database.

The inclusion criteria for participants were age >18 years (male or female), first- or second-time recipient of a functioning solitary kidney transplantation performed 6 weeks to 60 months earlier, legally competent, assent provided by the transplant physician so that the patient is able to participate, patient prescribed ≥3 medications for immunosuppression and hypertension, electronic pill tray–based medication adherence score <0.85 across a 1-month screening period, uncontrolled systolic hypertension (SBP ≥130 mm Hg) at the screening visit and baseline evaluation (following 1-month medication monitoring period), and 24-hour ambulatory SBP ≥130 mm Hg following the medication monitoring period.

The exclusion criteria were severe cognitive impairment/dementia; inability to self-administer medications, self-measure BP, or use a mobile phone; poor cellular coverage at home; inability to speak, hear, or understand English; history of psychiatric illness or substance abuse; planned pregnancy; and vulnerable populations such as pregnant or nursing women, prisoners, and institutionalized individuals.

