### Outcome Measures

#### Primary Outcome Measures

These include proportion of participants achieving success in meeting and sustaining adherence to the KDIGO guidelines for SBP control (resting SBP <130 mm Hg) and proportion of participants meeting and sustaining monthly medication adherence scores >0.90.

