### Proposed Sample Size

To evaluate SMASK treatment efficacy, 80 patients will be recruited and randomly assigned to either SMASK or SC. The primary outcomes of aim 1 include the proportion of patients with >0.90 medication adherence scores (based on the date/time stamped scores from the electronic trays) and proportion of patients meeting and sustaining adherence the KDIGO guidelines for clinic-based SBP control (<130 mm Hg). In intent-to-treat (ITT) analysis, with 40 patients per group, a two-sided Chi-square test (α=0.05) will have >90% power to detect a difference of 35% in proportions of those who are medication adherent (or meeting and sustaining adherence to the KDIGO BP guidelines) in the SMASK group compared to those in the SC group at the 3-month time point. A difference of 35% in medication adherence between the groups would be considered clinically relevant and warrant changes in clinical practice. Conservative estimates for medication adherence and expected BP control proportions will be used for power calculations. This approach was taken with a small pilot study, and CIs on effect sizes were quite large. Medication adherence observed in the SMASK 3-month feasibility study was 89% (versus 0% in control group; N=19). For the clinic resting BP control, we observed that 90% versus 10% of the participants controlled BP in the SMASK and control groups, respectively. Overall attrition was 10% in the intervention group [69].

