### Statistical Analyses

#### Primary Outcome Measures

The ITT analysis set will be determined in accordance with the International Conference on Harmonization E9 Guideline “Statistical Principles for Clinical Trials” [70] and will include all randomized subjects. For all subjects included in the ITT analysis set, all available data points will be included in the model. We chose a mixed-effects model approach because this method is a standard method in RCTs and can handle missing data and account for correlated data such as repeated measurements within patients or patients clustered within providers [71-73].

We propose a two-level analysis strategy: Our primary analysis will include the simple mixed-effects model containing the fixed time and intervention group, time, and time-by-intervention as primary independent variables (fixed effects) and MD as a random effect to account for clustering. The main analysis will compare the two intervention groups (SMASK vs SC) at the primary time point outcome at 3 months. We will estimate medication adherence score changes and changes in resting and 24-hour BP for each subject over the trial (preintervention and 1, 3, 6, and 12 months) and the within-subject longitudinal trajectories (eg, slopes) and summarize the mean longitudinal trajectory within each group. Intraclass correlations and variance estimates will be obtained for the efficacy outcomes and covariance structure of the longitudinal scores to determine the sample size (and hence adequate power) for a future effectiveness RCT.

In secondary/exploratory analysis for aim 1 outcomes, the potential influence of *a priori* specified covariates on these models will be explored, including self-determination theory tenants, demographic and clinical characteristics, and comorbidities. In an additional exploratory analysis, effect modifications of covariates will be examined through inclusion of covariate-by-group interaction terms in the multivariable models.

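### Both primary outcomes are proportions powered by a chi-square test at 3 months, but the primary-analysis paragraph names no binary dependent variable and lists only score and blood pressure changes.

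*Protocol article*

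**What the plan says.** The Outcome Measures section defines two primary outcomes, both binary per patient. For blood pressure it is the "proportion of participants achieving success in meeting and sustaining adherence to the KDIGO guidelines for SBP control (resting SBP <130 mm Hg". For adherence it is the "proportion of participants meeting and sustaining monthly medication adherence scores >0.90". The Abstract also describes both as proportions.

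Proposed Sample Size keeps to that form. It says that, "with 40 patients per group", "a two-sided Chi-square test (α=0.05) will have >90% power to detect a difference of 35% in proportions" of patients who succeed "in the SMASK group compared to those in the SC group at the 3-month time point".

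The Statistical Analyses section, under Primary Outcome Measures, describes a mixed-effects model with group, time and their interaction as fixed effects and the physician as a random effect. It makes the 3-month comparison of the arms the main analysis but does not say what the dependent variable is. The next sentence gives the quantities: "We will estimate medication adherence score changes and changes in resting and 24-hour BP for each subject over the trial". It lists the preintervention visit and months 1, 3, 6 and 12, and adds within-subject trajectories with slopes as an example.

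Study Participants requires a tray score below 0.85 over the screening month and "uncontrolled systolic hypertension (SBP ≥130 mm Hg) at the screening visit and baseline evaluation".

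**The concern.** A proportion below 130 mm Hg and a mean change in mm Hg are different quantities. So are a proportion above 0.90 and a mean change in score. The article declares and powers one kind and, in the paragraph meant to analyse it, describes the other. Anyone following that paragraph could report a mean change as the primary result, or dichotomise, and call either one planned. The choice could then be made with the data in view.

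Reading the model as a logistic one does not fully settle it. The visit list includes the preintervention visit, at which nobody eligible can be a success on either outcome. That affects some terms of the time-by-group model, including the interaction that the paragraph lists among its primary independent variables.

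**Working it through.** **1. The plan's power figure.** Inputs from Proposed Sample Size: n = 40 per arm, two-sided α = 0.05, difference δ = 0.35. The control proportion is not given (the text says only "Conservative estimates for medication adherence and expected BP control proportions will be used for power calculations"), so I assume a range of 0 to 0.60.

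Pooled formula: power = Φ[(δ − 1.96·SE0)/SE1], with SE0 = √(2p̄(1−p̄)/n) and SE1 = √([p1(1−p1) + p2(1−p2)]/n).

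Least favourable pair, 0.325 versus 0.675: SE0 = 0.1118, SE1 = 0.1047, and (0.35 − 0.2191)/0.1047 = 1.25, so Φ = 89.4%.

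| Control vs SMASK | Pooled formula | Exact chi-square |
|---|---|---|
| 0% vs 35% | 99.3% | 99.99% |
| 10% vs 45% | 95.4% | 96.0% |
| 32.5% vs 67.5% | 89.4% | 90.4% |

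The stated figure of more than 90% is essentially reproduced, for a comparison of two proportions.

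**2. The sections side by side.**

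| Section | Quantity | Method |
|---|---|---|
| Outcome Measures | Proportion succeeding | not given there |
| Proposed Sample Size | Proportion succeeding, month 3 | Chi-square |
| Statistical Analyses, primary | Changes in score, resting BP and 24-hour BP; trajectories | Mixed-effects model, dependent variable not named |
| Statistical Analyses, exploratory | Adverse event proportions | Chi-square |

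Within Statistical Analyses, chi-square appears only for adverse events. Two details suggest that the primary paragraph was not written around the declared endpoints. It includes 24-hour BP, which Outcome Measures makes exploratory. It also applies one visit list to everything, whereas Table 1 shows no tray-based adherence at 12 months and no ambulatory BP at 1 or 3 months.

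**3. How far apart the two quantities are.** Assume SBP is normal with the same SD in both arms, between 12 and 20 mm Hg (an assumption; the article gives no SD). Control rates of 32.5% and 67.5% then correspond to a mean difference of SD × [z(0.675) − z(0.325)] = SD × 0.908, or 10.9 to 18.2 mm Hg. The power of a comparison of means is Φ(0.908/√(2/40) − 1.96) = Φ(2.10) = 98%, against 89.4% for the proportions. The power statement therefore does not describe a mean-change analysis. The problem is a different question, not a shortage of power.

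**4. The binary reading with the preintervention visit kept in.** Take visit as a factor and an illustrative 35-point difference at month 3:

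| | SC | SMASK |
|---|---|---|
| Baseline | 0/40 | 0/40 |
| Month 3 | 4/40 | 18/40 |

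The model is logit p = β0 + β1·group + β2·time + β3·group×time. Both baseline log odds are minus infinity, so:

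- β1, the baseline group contrast, is the difference of two infinities and is undefined.
- β2, the time term, is ln(4/36) minus minus infinity and is infinite.
- β3, the interaction, is the month-3 log odds ratio minus β1 and is undefined.

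Software still prints an interaction of 2.0 with SE 29,295. That SE only reflects where the iterations stopped. In a second illustrative table (10/40 versus 24/40 at month 3), the time coefficient is 10.5 after 10 iterations and 23.5 after 25, and the interaction SE goes from 44 to 29,295.

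The month-3 contrast β1 + β3 uses only the month-3 cells:

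- log OR = ln(18/22) − ln(4/36) = −0.20 + 2.20 = 2.00
- SE = √(1/18 + 1/22 + 1/4 + 1/36) = 0.615
- z = 3.24, p = 0.001

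This fit omits the physician random effect. With time as a straight line over several visits the terms would be finite, but the line would still be tied to a visit whose success rate eligibility sets at zero.

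**The case against.** The strongest reply is that the article already fixes what matters. It names the contrast (SMASK versus SC) and the time point (3 months), and a mixed-effects model may be logistic. The link function is commonly left to a statistical analysis plan, which is not shown here. The sentence about changes comes after the main-analysis sentence and can be read as a wider longitudinal description leading to variance estimates for a future trial.

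Much of this stands. That the primary model is continuous is an inference from the quantities listed, not something the article states. A missing link function alone would be no finding. What remains is that the stated text conflicts: the outcome is a proportion, and the section analysing it lists only changes.

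Stronger readings are tempting but not supported:

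- **That the primary endpoint has no workable test, or that a 35-point difference would give p near 1.** That follows only if the interaction coefficient is taken as the test. The article's main comparison is at 3 months, and that contrast is intact (p = 0.001 above).
- **That a slope over 0 to 12 months would dilute or reverse the effect.** Slopes are only an example of a trajectory to be summarised within each group. No between-group slope test is declared primary.
- **That sustained success is meaningless at month 3.** The adherence outcome uses monthly scores and the tray records daily, so three monthly scores exist by then. Resting SBP is measured at months 1 and 3. The term is undefined in the article, not empty.
- **That a zero cell at month 3 is likely.** The 0% adherent controls come from a pilot of 19 patients. With a true rate of 5%, the chance of 0/40 is 0.95^40 = 13%; at 10% it is 1.5%.

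**Conclusion.** The mismatch holds. The article declares and powers two binary outcomes at month 3, and its primary-analysis paragraph states no analysis that matches them. Binary and continuous readings are both open, and they answer different questions.

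The baseline visit is a narrower problem. It arises only if the time-by-group model is fitted to the binary outcomes with the preintervention visit as a response. With visit as a factor, the time, baseline-group and interaction terms are then inestimable by design, while the month-3 group contrast survives. For continuous changes, a baseline value is legitimate.

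The sample size is not in question here. With 40 analysed per arm, power for the binary comparison is 89.4% or more by the pooled formula and at least 90.4% exactly, across assumed control rates of 0 to 0.60.

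**What to change.** Reword the primary-analysis paragraph so that it:

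- names the between-group comparison of each binary outcome at month 3 as the primary test, for example a risk difference with 95% CI, or logistic regression with baseline SBP or baseline score as a covariate (the choice among sound methods is the sponsor's);
- restricts any repeated-measures model of the binary outcomes to post-baseline visits;
- labels the analyses of score change, BP change and trajectories as supportive, and leaves 24-hour BP with the exploratory outcomes;
- states what sustained success means at month 3, for instance which monthly scores and which clinic visits must all be successes.

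If an analysis plan already says this, the article's text should be brought into line with it. The cost is rewording, with no new data and no change in sample size. The article's Results section reports only baseline data under analysis, so at that stage the choice could still be fixed before the arms are compared.

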#### Secondary Outcome Measures

Secondary outcome measures of changes in self-determination theory tenants (self-efficacy and autonomous self-regulation) and provider adherence to KDIGO guidelines (timing of medication changes) will be investigated using mixed effects models with these outcomes as separate dependent variables, group (SMASK vs SC) as primary independent variable, and the primary outcomes (medication adherence and clinic SBP) and clinical and demographic characteristics as adjustment variables.

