**Methods:**

This two-arm, 6-month, phase II single-site efficacy RCT will involve 80 kidney transplantation recipients. Participants will be randomly assigned to the SMASK intervention arm or control arm. SMASK includes multilevel components: automated reminders from an electronic medication tray; tailored text messages and motivational feedback, guided by the self-determination theory; and automated summary reports for providers. Evaluations will be conducted preintervention, at 3 and 6 months, and posttrial at 12 months. Specific aims are to test the hypotheses that compared to standard care, the SMASK cohort will demonstrate significantly improved changes at 3, 6, and 12 months in the primary outcome variables medication adherence (proportion with electronic monitor-derived score >0.90) and blood pressure control (proportion meeting and sustaining adherence to the Kidney Disease Improving Global Outcomes [KDIGO] guidelines for blood pressure control); the secondary outcome variables provider adherence to KDIGO guidelines, measured by timing of medication changes and changes in self-determination theory constructs; and the exploratory outcome variables estimated glomerular filtration rate, variability in calcineurin inhibitor trough levels, and proportion of patients meeting and sustaining the 24-hour ambulatory blood pressure below 130/80 mm Hg. After the 6-month evaluation, interviews with a random sample of SMASK subjects (n=20) and health care providers (n=3-5) will assess user reactions including acceptability, usability, and aids/barriers to sustainability. Data from the RCT and interviews will be triangulated to further refine and optimize SMASK and prepare for a multisite effectiveness RCT.

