
This paper describes a 6-month efficacy RCT with a 6-month posttrial follow-up, utilizing a further refined SMASK mHealth system in kidney transplant recipients verified to be medication nonadherent with poorly controlled hypertension. The aims of this study are twofold: (1) to assess the efficacy of our mHealth system for monitoring and enhancing medication adherence and BP control during the 6-month active trial and the 6-month post-trial follow-up period and (2) to evaluate provider adherence to BP management guidelines and changes in participants’ levels of self-efficacy and autonomous motivation to sustain engagement in the medical regimen over time. Exploratory outcome variables will include changes in eGFR and variability of calcineurin inhibitor (CNI) trough levels (%cv).

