Participants will be sent SMS messages every 3 days as a reminder to measure their BP with the Bluetooth-enabled A&D UA-767 Plus BP monitor (A&D Medical, San Jose, CA). They will be instructed to measure their BP in the morning and evening every third day by using our resting BP protocol (described under Clinic Resting Blood Pressure). They will also receive a tailored positive reinforcement SMS message the day after successful completion of their BP measurements. An app will be installed on their smartphone, which will securely receive and transmit the BP data to the MUSC-housed server. The app will also provide text instructions throughout the BP protocol and a video clip module demonstrating use of the app and the BP monitor.

A weekly SMASK dashboard summary report, tailored to the treating physician’s preferences, will be delivered via email (Figure 3). The report will summarize each subject’s medication adherence and adherence to the BP self-monitoring schedule for the prior 2 weeks. Color coding will be used to indicate where the subject lies relative to the desired goals (ie, SBP <130 mm Hg and adherence score >0.90). In addition, a breakdown of the BP readings obtained over the 2 weeks will be provided with systolic and diastolic pressures. The treating physician will make adjustments to the medical regimen, as indicated and guided by the KDIGO guidelines [49]. The physician will notify the study coordinator of the changes via email. Any medication changes made by the treating physician will be mirrored in the programming of the medication tray after the study coordinator confirms with the patient that the changes have been enacted. The research manager and staff will be contacted via email, and the SMASK participants will be contacted via their preferred mode (SMS, email, or phone) when they fail to measure BP or when the measured BP is outside of the threshold ranges established by the treating physician, or they will be contacted via an SMS text when the SimpleMed+ tray identifies lack of medication adherence.

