### Active Trial Evaluations and Follow-Up Phase

All subjects will be followed up for an additional 6 months following the 6-month active trial. Patients will continue to attend the clinic at a frequency determined by the provider. At 1, 3, 6, and 12 months after randomization into the SMASK or SC group, subjects will be assessed on medication adherence using medication possession ratio checks, clinic resting BPs, and completion of a brief set of questionnaires including measures to assess self-determination theory tenants of autonomous self-regulation and self-efficacy (Table 1). Providers are assessed on adherence to BP management protocols and goals. The timeliness and appropriateness of medication changes will be evaluated according to KDIGO guidelines across both groups at the conclusion of the study.

**Table 1 table1:** List of measures and evaluation time points.

Outcome variables		Measurements/instruments used	Screening	Baseline	1 month	3 months	6 months	12 months

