**Secondary outcomes**								
	Therapeutic Inertia	Provider adherence to KDIGO^c^ goals: Timely medication changes (date of medication change following medication adherence) and BP feedback (biweekly SMASK^d^ reports for SMASK participants) and from clinic visits for all subjects (Figure 2)	Weekly^e^	Weekly^e^	Weekly^e^	Weekly^e^	Weekly^e^	Weekly^e^
	Self Determination Theory Constructs	TSRQ^f^ autonomous self-regulation [51,52] (α=0.81-0.84; correlation with GCOS^g^: *r*=0.38, *P*<.001; correlation with HCCQ^h^: *r*=0.38, *P*<.001), weight loss attendance (*r*=0.34, *P*<.001), body mass index (*r*=-0.11, *P*<.05), 18-month test-retest autonomous (*r*=0.47), controlled items (*r*_s_=0.34]) [53], correlation with medication adherence (*r*=0.58, *P*<.001)] [54]	✓			✓	✓	✓

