#### Secondary Outcome Measures

These include provider adherence to KDIGO guidelines, as measured by the appropriateness and timeliness of BP medication changes, and subjects’ self-report of changes in self-determination theory tenants (ie, self-efficacy and autonomous motivation).

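### Provider adherence to KDIGO is defined by appropriateness and timeliness of BP medication changes, but the only stated between-group analysis models timing alone

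*Protocol article*

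**What the plan says.** The protocol article describes this outcome in several places, in two ways.

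**Two components.** Under Outcome Measures, Secondary Outcome Measures, the outcome is "provider adherence to KDIGO guidelines, as measured by the appropriateness and timeliness of BP medication changes". Active Trial Evaluations and Follow-Up Phase commits to judging both: "The timeliness and appropriateness of medication changes will be evaluated according to KDIGO guidelines across both groups at the conclusion of the study".

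**Timing only.** Under Statistical Analyses, Secondary Outcome Measures, the text reads "provider adherence to KDIGO guidelines (timing of medication changes) will be investigated using mixed effects models". Group is the main independent variable there. The two primary outcomes and clinical and demographic characteristics are adjustment variables. The abstract gives "provider adherence to KDIGO guidelines, measured by timing of medication changes". The Therapeutic Inertia row of Table 1 lists "Timely medication changes (date of medication change following medication adherence) and BP feedback", with the SMASK reports as a source for SMASK participants, "and from clinic visits for all subjects".

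The second aim in the Introduction is "to evaluate provider adherence to BP management guidelines", with no restriction to speed. The description of the SMASK system says: "The treating physician will make adjustments to the medical regimen, as indicated and guided by the KDIGO guidelines".

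**The concern.** Guideline adherence in prescribing has at least two parts: whether the change made was the right one, and how soon it was made. The article recognises both in its definition, and its account of the intervention has physicians act when a change is indicated. The model, however, is given only the second part as its dependent variable.

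What is at stake is the label on the result. If physicians changed drugs sooner in the SMASK arm, the stated analysis would allow this to be reported as better adherence to KDIGO, although nothing in the model had asked whether the changes agreed with KDIGO. With two definitions in the text, the choice between them could also be made after outcome data are seen.

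The outcome is secondary. The sample size and the primary comparisons do not depend on it.

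**Working it through.** The plan states no figure for this outcome, so there is none to reproduce. The main check is to set the places that define, measure or analyse it side by side.

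| Place in the protocol article | Appropriateness | Timeliness | Between-group model stated |
|---|---|---|---|
| Outcome Measures, Secondary | yes | yes | no |
| Active Trial Evaluations and Follow-Up Phase | yes | yes | no (an evaluation in both groups is promised, no method) |
| Abstract, Methods | no | yes | no |
| Table 1, Therapeutic Inertia | no | yes | no |
| Statistical Analyses, Secondary | no | yes | yes (mixed effects model) |

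Both places that name appropriateness stop short of a model, and the one place that gives a model names timing. The provider interviews under Qualitative Studies touch on therapeutic inertia, but they ask about the SMASK program and do not compare the arms, so they do not fill the gap.

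The second check is what an added comparison of appropriateness could show. For a difference between two proportions with *n* patients per arm, *m* scored decisions per patient and within-patient correlation ICC:

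half-width of the 95% CI = 1.96 × √( 2 × p(1 − p) × [1 + (m − 1) × ICC] / (n × m) )

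Inputs:
- n = 40 per arm, from Proposed Sample Size.
- n = 36 per arm as an alternative: 40 × 0.90. The same section gives 10% attrition for an intervention group; applying it to both arms is an assumption.
- p = 0.5 in both arms, an assumption that gives the largest binomial variance.
- m = 1 or 4, an assumption, because visit frequency is left to the provider.

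Results:
- n = 40, m = 1: 1.96 × √(0.5 / 40) = 0.219.
- n = 36, m = 1: 1.96 × √(0.5 / 36) = 0.231.
- n = 40, m = 4, ICC = 0: 1.96 × √(0.5 / 160) = 0.110.
- n = 40, m = 4, ICC = 1: 0.219, the same as one decision per patient.

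These figures contain no term for clustering by physician, which the primary analysis expects and models with a physician random effect. If physicians align with arms, the intervals would be wider. The figure of about 22 points is therefore an indication and not an upper bound. It describes the precision of the proposed addition, not the size of an error in the trial.

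**The case against.** The strongest reply is that this is a matter of labels. The dependent variable in the analysis section is provider adherence to KDIGO guidelines, and timing stands in a parenthesis that could be shorthand. The follow-up section promises an evaluation of both components in both groups. A condensed article may leave the scoring rule and the model for appropriateness to a full protocol or analysis plan that is not shown.

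Part of this stands. A reader might infer that appropriateness has been dropped or will never be compared between the arms. The documents do not support that, because the evaluation across groups is still promised. The missing scoring rule is no finding either. What remains is that the text fixes the dependent variable more narrowly in one place than it defines the outcome in another. A fuller document could follow either version, and the article does not say which governs.

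A second tempting inference is that timing alone would count a rightly withheld change as delay. The article nowhere says that an occasion with no indicated change is scored as delay, and it judges timeliness against KDIGO. That reading rests on silence. For the same reason there is no firm ground for restricting timing to occasions on which a change was indicated. That subset would arise after randomisation.

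It is also fair to object to any scoring rule that denies credit for reasons found only in the SMASK report. Holding back escalation when the report shows missed doses is behaviour that the intervention intends, and such a rule could bias the comparison against SMASK. The remedy should not include one.

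Finally, the contradiction could be removed in the other direction, by dropping appropriateness from the definition. That is legitimate if the result is then named for what it measures.

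**Conclusion.** The point holds as an internal contradiction about a secondary outcome. Two components are defined and promised for evaluation in both groups; one has a stated between-group analysis. The consequence is that a timing result could be presented as guideline adherence. Whether this would favour either arm, and by how much, cannot be told from the documents. Primary conclusions and sample size are unaffected.

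A comparison of appropriateness would be imprecise: about 22 points half-width with 40 per arm and one decision each, and about 23 points with 36 per arm, before any provider clustering. These figures rest on the assumed 50% in both arms and the assumed number of decisions. The comparison should be read as descriptive. It is still worth making, because without it the second aim is not answered as the article itself defines the outcome.

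**What to change.** In Statistical Analyses, Secondary Outcome Measures:

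1. Replace the parenthesis after the outcome's name with two separate dependent variables: timeliness of BP medication changes, and appropriateness of BP medication changes, each judged against KDIGO as the follow-up section already plans.
2. Analyse appropriateness as a yes/no outcome in a logistic mixed model with patient and physician random effects, the latter as in the primary analysis.
3. Compare the arms by randomised group without adjusting this comparison for medication adherence and clinic SBP. Both are measured after randomisation and both are what SMASK is meant to change.
4. Bring the abstract and the Therapeutic Inertia row of Table 1 into line.

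If appropriateness cannot be scored, remove it from Outcome Measures and from the follow-up section, and report the result as timeliness of medication changes only, not as guideline adherence.

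The cost is one added model, a written scoring rule and aligned wording. The judgement itself is already planned for both groups. The Results section says that baseline data were being analysed when the article was written, so the rule could at that point still be fixed before outcome analysis. The downsides are low precision and the chance that chart notes reveal the arm to assessors who are meant to be blinded.
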